**5.3 Pilot Study**

The data collection instruments, the classification/diagnostic tool and study procedures will be evaluated in a pilot study of at least 2 patients per catchment area. The case report forms, diagnostic tool and study procedures will be modified as necessary based on the results of the pilot study. The data collected during the pilot study will not be used for final analyses and therefore have not been included in the sample size.

**5.4 Data Management**

Data collectors will report to data supervisors. There will be two data supervisors; each will have responsibility for coordinating six data collectors. Each supervisor will make contact with each of the six data collectors he is responsible for, and collect all recently completed case report forms at that time. They will check the forms to ensure that they are completed properly and that there are no blanks. The data supervisors will in turn coordinate with the data manager who will be responsible for double entry of the data into a computer data base. The data manager will run consistency and validations checks and generate errors. The data supervisors will be notified of missing, ambiguous, or non-interpretable data entry on the forms so that these queries can return down the chain back to the responsible data collector for clarification or reconciliation. Once these forms are finalized, primary data analysis will be performed to track accrual and event statistics, and to identify systematic errors that are occurring in the data entry and/or collection process in a timely fashion. The data manager will in turn interface with the chief statistician on the project at BUSPH for the purposes of final data cleaning and analysis.

**5.5 Performance Assessment**

The performance of CHWs will be assessed through two methods on a quarterly basis. The first will be done through the quarterly analysis of the information recorded on the identification and baseline form. From this data, we will be able to determine the CHWs’ performance in classification and treatment. For classification, we will calculate the “percentage of misclassification” (number misclassified based on the complaints out of the total number classified multiply by 100). For treatment, we will calculate the “percentage of inappropriate treatment” (number inappropriately treated based on classification out of the total number classified multiply by 100). Percentage of misclassification or inappropriate treatment of more than ten percent will be considered unacceptable. Such CHW will receive remedial education, which will be arranged by the field coordinator. The second method of assessment will be carried out by the supervisors (rural health center staff or the CHS mobile team) during a normal supervisory and supportive visit. The supervisors will assess the performance of CHWs by observing them attending to patients at the community health post including performance and interpretation of RDTs. If supervisors realize that there are not enough patients for observation at the community level, CHWs may be brought to the health facility and given patients to attend to in order to assess their performance. The supervisor will report the performance as “satisfactory” or “not satisfactory” on the supervisory checklist depending on the CHWs ability to classify and provide the appropriate management or perform and interpret RDTs. This information will be captured on the Health Facility Data Capture Form. CHWs with “unsatisfactory” performance will receive remedial education.

**5.6 Measurement of economic costs**

###### Types of costs measured

The data collectors will obtain economic indicator data to allow us to estimate the total direct costs associated with the intervention, the difference in costs between the intervention and control groups, and the cost-effectiveness of the intervention. This will involve collecting data on two major categories of direct costs, and at different levels, as follows:

1) *Direct medical costs*: those medical costs related to diagnosis and treatment of malaria at the household, CHW and health facility levels, including facility-based overhead/administration, personnel time, bed fees, medications and supplies, diagnostic tests, and outpatient consultations.

2) *Direct non-medical costs*: those costs unrelated to medical care, including transportation, meals, and other expenses associated with diagnosis and treatment seeking, as well as training costs, non-medical supplies and materials, and community education/sensitization activities.

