#### 4.18 Economic Analyses

The overall goal of the economic evaluation is to determine the cost effectiveness and the difference in economic costs between the use of RDTs in the diagnosis and treatment of malaria (the intervention) and the presumptive treatment of fever with Coartem (the control). The economic analysis will also determine the incremental cost-effectiveness of the use of RDTs in the diagnosis and treatment of malaria so as to provide an additional measure by which to judge the usefulness of the ZIMMAPS intervention. The economic analyses will be based both on cross sectional data collected from health facilities and data collected longitudinally from the caretakers of ill children. The key indicators will be direct economic costs incurred in both the treatment and control areas. We will measure such costs at the household, health care provider, and medical facility levels related to diagnosis and treatment of malaria and pneumonia by CHWs, including referrals. Health outcome will be measured as treatment failure defined earlier.

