The data collectors will visit the CHWs at least every other day to collect completed identification and baseline forms to schedule a follow-up visit. The DC will check with the CHW register to ensure that every child seen by the CHW with fever of fast breathing has a completed identification and baseline form. The follow-up visits will be made at 5-7 days after the caregiver visits the CHW. Information that will be collected during the Day 5 – 7 follow-up visits will include, complaints that prompted heath seeking at the CHW, whether rapid diagnostic test was done, treatment given, counseling or advice given, self-reported adherence to the medication, outcome of the visitation, alternative treatment after the visit and where such alternative treatment was obtained, current general condition and complaints and results of temperature and respiratory rate taken.

Economic cost data from health facilities will be collected by the data collectors. These data will include the average costs associated with treating uncomplicated and severe cases of malaria and pneumonia, including overhead, equipment, personnel, medicines, and supplies. This information will then be matched with the case records in order to estimate the facility-based costs of treatment for children in intervention and control groups.

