# 6.3 Analysis of economic outcomes

###### Univariate and multivariable analyses

Analyses will be conducted at the provider level (encompassing both households and facilities). We will calculate the mean costs of diagnosis and treatment of malaria pneumonia for intervention and control groups, their standard deviations, medians, and ranges. Group differences in costs will be assessed using chi-square tests. Univariate analyses will also be conducted for likely predictors of costs, including household socio-demographic characteristics (i.e., education of mother, household size), distance from household to nearest health facility, and treatment history details (i.e., referral to RHC, time from diagnosis to RHC visit, follow-up on referral, hospitalization).

We will conduct multivariate regression to estimate the effect of various factors, including household socio-demographic characteristics and study arm, on the total cost by day 5-7 of treatment of malaria.

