###### Estimate of incremental cost per health outcome

Several of our specific secondary objectives will involve calculating cost-effectiveness ratios (CERs). Each CER will be estimated by calculating the difference in costs divided by the differences in health outcome according to the following standard cost-effectiveness formula:

*CER = (CA – CB) / OA – OB),*

Where C refers to total cost, O refers to outcome, A refers to the intervention group, and B refers to the control group.

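### The cost-effectiveness ratio has no fixed disease scope: direct medical costs in 5.6 and the 6.3 regression are malaria-only, 4.18 and 5.1 cover malaria and pneumonia, and the outcome covers all treated children

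*Protocol*

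**What the plan says.** The protocol sets the scope of costs in several places.

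- **4.18 Economic Analyses** will measure costs "related to diagnosis and treatment of malaria and pneumonia by CHWs, including referrals". It takes treatment failure as the health outcome.
- **5.1 Data Collection** has data collectors obtain from health facilities the "average costs associated with treating uncomplicated and severe cases of malaria and pneumonia".
- **5.6, Types of costs measured**, limits direct medical costs to "those medical costs related to diagnosis and treatment of malaria at the household, CHW and health facility levels". Direct non-medical costs carry no disease limit; they include travel, meals and "other expenses associated with diagnosis and treatment seeking, as well as training costs".
- **6.3, Univariate and multivariable analyses**, compares the "mean costs of diagnosis and treatment of malaria pneumonia for intervention and control groups" (a conjunction seems to be missing), then models the effect of study arm and other factors "on the total cost by day 5-7 of treatment of malaria".
- **6.3, Estimate of incremental cost per health outcome**, defines the CER with the words "Where C refers to total cost, O refers to outcome", and names no disease.
- **3.5 Secondary Outcomes** defines treatment failure over treated children without a disease limit, and counts additional antibiotics as well as additional antimalarials as failure. Its cost items include training, RDT kits, Coartem and referral, but do not name amoxicillin.

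**The concern.** A CER is interpretable only if its cost difference and its outcome difference refer to the same care in the same children. Here a reader who follows 4.18 and a reader who follows 5.6 would put different costs into C, while O stays the same.

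The part in dispute does not cancel between arms. Under 4.2, suspected pneumonia is treated with amoxicillin at the post in the intervention arm and referred to a facility in the control arm. The first secondary hypothesis in 3.3.2 attributes the expected fall in treatment failure partly to community pneumonia treatment replacing referral. A malaria-only C could therefore leave out the medical cost of care whose health effect is counted in O.

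Cost-effectiveness is a named secondary objective, and 9.5 expects the results to bear on national policy.

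**Working it through.** The protocol states no cost, CER or cost-per-outcome figure, so there is nothing to reproduce. The check is a comparison of definitions.

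| Section | Element | Disease scope |
| --- | --- | --- |
| 4.18 | Costs to be measured | Malaria and pneumonia, with referrals |
| 5.1 | Facility cost data | Malaria and pneumonia |
| 5.6, item 1 | Direct medical costs | Malaria only |
| 5.6, item 2 | Direct non-medical costs | No limit |
| 6.3 | Mean-cost comparison | Both named |
| 6.3 | Regression outcome | Malaria only |
| 6.3 | C in the CER | Not stated |
| 4.18 with 3.5 | O in the CER (treatment failure) | All treated children |

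To see what depends on the choice, write each arm's total cost as three parts: M, medical costs of malaria care; P, medical costs of pneumonia care; N, non-medical costs. This assumes that medical items can be assigned to one disease. A is intervention and B is control, as in 6.3.

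1. Scope of 4.18: CA − CB = (MA − MB) + (PA − PB) + (NA − NB).
2. Scope of 5.6: CA − CB = (MA − MB) + (NA − NB).
3. Difference between the two: PA − PB.
4. OA − OB is the same in both cases, so the two CERs differ by (PA − PB) / (OA − OB).

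That term vanishes only if pneumonia medical costs are equal in the two arms. By design, PA is mainly amoxicillin given at the post and PB is mainly facility care after referral, so equality would be a coincidence.

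No value can be put on the term. The protocol gives no unit cost for either component, and 3.6 treats compliance with pneumonia referral as something to be measured, so the number of control children who incur facility costs is unknown as well.

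One further unevenness lies inside 5.6: training is counted in full under item 2 and, by 4.7, covers both diseases, while pneumonia medical care falls outside item 1.

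**The case against.** The best defence is that the malaria limit is deliberate. The cost-effectiveness objective in 3.3.1, its hypothesis in 3.3.2, the listing in 6.2 and the goal sentence of 4.18 all compare Coartem with and without RDTs, which is a question about malaria and fever. That stands, and it means that costing both diseases is not the only legitimate repair. It does not remove the conflict. A malaria-only ratio needs a matching outcome, and 4.18 uses treatment failure as defined in 3.5, over all treated children. On either reading some section must change.

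A second defence is that the plan, read as a whole, already covers both diseases. 5.6 opens by referring to the total direct costs of the intervention, which includes amoxicillin; the CER does not point to item 1 of 5.6; and facility costs for both diseases are collected, so the scope could be settled at analysis. This stands in part: the mismatch is left open by the text, not planned. But 5.1 secures pneumonia costs only at facilities. Item 1 of 5.6, read literally, does not call for pneumonia medical costs from households or CHWs, and these may be hard to recover later.

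Two stronger readings should be resisted. A reader might infer that 5.6 and 6.3 are malaria-only throughout. They are not: the mean-cost comparison in 6.3 names both diseases, and the limit in 5.6 applies to medical costs only. A reader might likewise infer that all pneumonia referral costs are lost under 5.6. Travel and meals are not excluded there, and 3.5 lists referral cost; the clear omission is medical care for pneumonia.

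**Conclusion.** The inconsistency is real and should be corrected. Direct medical costs in 5.6 and the regression outcome in 6.3 are narrower than the costs in 4.18, 5.1 and the 6.3 mean-cost comparison, and the CER does not say which applies. If the 5.6 definition is used, cost and outcome cover different care, and the CER shifts by (PA − PB) / (OA − OB).

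The size and direction of that shift are unknown. A reader might infer that the sign of the incremental cost could reverse; without unit costs the documents do not support that. A reader might also scale the problem by the planned numbers, 524 / (524 + 1518) = 26% of children with fast breathing. That is unsound: the eligibility text allows a child to have both fever and a respiratory complaint, so the two groups can overlap, and both figures are power-based targets, not case shares.

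The point concerns one secondary economic outcome. No primary endpoint, sample size or safety analysis depends on it.

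**What to change.** State one disease scope in 4.18, 5.6 and 6.3, and compute C and O in the same children.

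- **If the CER uses treatment failure in all treated children:** extend item 1 of 5.6 and the regression outcome in 6.3 to malaria and pneumonia. Count medical costs of both, including referral, for households, CHWs and facilities in both arms.
- **If a malaria-only CER is kept to match the objective in 3.3.1:** restrict its outcome to febrile children and count all their treatment costs. Keep febrile children who also have fast breathing, since they too incur malaria costs; leaving them out would open a new mismatch.

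In either case, say in 6.3 which cost definition C takes. The cost is mainly wording, plus a little more cost data from households and CHWs. Facility pneumonia costs are already to be collected under 5.1. The change should be made before the case report forms are final.

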###### Cost measurement

Costs will be estimated on the basis of their resource value. Costs will be estimated using both information provided by caretakers on specific treatment seeking activities and estimates of associated costs at medical facilities. These facilities will include Chikankata hospital, rural health care centers, and CHW health posts. We will estimate the cost of overhead/administration (where not included in the bed fee) with the assistance of facility staff and other available data, as well as the costs associated with facility services, including personnel time, medications, diagnostic tests, and supplies.

The costs of non-facility provided medications, diagnostic tests, supplies and other medical items will be valued at their market cost, as will direct non-medical expenses paid by caregivers such as meals and transportation.

At the program level, the costs associated with implementing the intervention, such as training and materials, will be estimated on the basis of the costs of production and implementation of the intervention. All research-specific costs related to data collection will be excluded, as these are costs of the study and not of providing the intervention to the community. For example, any cost of supplying bicycles or motorized transportation for data collectors is a research-related cost that would not be incurred in actual implementation of the CHW intervention and thus would be excluded from the total cost of this intervention.

**6.0 Statistical Analyses**

# 6.1 Primary end-points comparison

There are two primary endpoints for the study depending upon whether a child has fever or fast breathing. For children with fever the primary outcome is appropriate treatment with Coartem® and for children with fast breathing the primary outcome is early and appropriate treatment. For each primary outcome, crude proportions in the two groups will be compared using the Mantel-Haenszel chi-square test with clusters as strata to account for the cluster randomization. Crude data will be presented as cluster adjusted odds ratios and 95% confidence intervals. Inferences about treatment effects will be made at the level of the individual not at the level of the cluster. Analyses will be based on an intent-to-treat basis.

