# 4.2 Study design

The study will be a cluster-randomized controlled trial. A study cluster will be defined as the catchment area of a community health post. CHWs work from a community health post with well defined catchment area and population within a health facility catchment area and are supervised by the staff of the health facility. The clusters (community health post catchment area) will be matched in pairs according to the health facility catchment area they belong to, the distance from the health facility and the population size. Randomization will then be done from among the matched clusters to select the intervention and the control arms. CHWs in both the intervention and control arms will receive training in the assessment and classification of children presenting with fever and/or cough/difficult breathing. The CHWs in the intervention arm will be supplied with RDTs, Coartem® and amoxicillin. The intervention CHWs will be trained to use RDTs in patients with reported fever and provide those with a positive result with Coartem while patients suspected of pneumonia (based on fast breathing) will be treated with amoxicillin as per the standard of care at health facilities and monitored. Those with negative RDT result will be treated with antipyretic and asked to return if they do not get better after 48 hours or condition deteriorates. In the control group, no RDT will be performed. The CHWs will be supplied with Coartem to treat malaria/febrile illness as per the IMCI guidelines and patients suspected of pneumonia will be referred to the health facility for treatment as per the current practice. The supply of the drugs and RDTs will come through the normal MOH sources. The study will utilize specialized field workers (data collectors and data supervisors) to visit CHWs to collect data on their consultations and follow-up children treated by CHWs. Consent will be sought from caregivers to allow us collect data by which to assess the effectiveness of the intervention. Caregivers in both the intervention and control arms are not obliged to receive care from the CHWs. They are free to go to any of the health facilities in the study area instead of a CHW. The study will collaborate with the MOH and the DHMTs to ensure that the health facilities in the study area have RDTs, Coartem and amoxicillin.

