**Treatment of children presenting with fever**

Currently 100% of children seen with fever should receive Coartem treatment. We hypothesize that with the use of an RDT, the proportion of children receiving Coartem treatment would be reduced to 80%.

**Sample size necessary to detect a 20% decrease of children not receiving Coartem for various ICCs**.

| Intracluster coefficient | Total Clusters | Sample per cluster | Total sample size |
| --- | --- | --- | --- |
| 0.05 | 38 | 2 | 76 |
| 0.07 | 40 | 2 | 80 |
| 0.09 | 42 | 2 | 84 |
| 0.11 | 34 | 3 | 102 |
| 0.13 | 36 | 3 | 108 |
| 0.15 | 36 | 4 | 144 |
| 0.17 | 36 | 5 | 180 |
| 0.19 | 38 | 6 | 228 |
| 0.21 | 38 | 12 | 456 |
| 0.23 | 40 | 33 | 1320 |
| 0.25 | 46 | 36 | 1656 |

At the largest ICC of 0.25, 46 clusters enrolling 36 subjects each for a total of 1656 subjects would be necessary to show a difference between the intervention and control arms. Since we do not have 46 clusters, and no feasible increase in subjects per arm will allow us to reduce the total clusters to 42, we would be underpowered with an ICC of 0.25. However, we would be able to meet the study enrollment needs at every other ICC. At the smallest ICC of 0.05, the total sample size would be only 76 subjects being recruited from 38 clusters with 2 subjects per cluster. Therefore, within these likely ranges of ICC we would need to enroll between 76 and 1320 subjects. Following the logic above we would enroll 1320 subjects. We anticipate a drop out rate of 15%; hence we will increase our sample size to 1518 children with fever.

All of the 49 CHWs supported by CHS will be used.

20 households per cluster will be selected through multi-stage sampling. 420 caregivers will therefore be interviewed. Since the household survey will be repeated at the end of the intervention, a total of 840 caregivers will be interviewed.

The total sample size for the study will be 2931 (524 + 1518 + 840 + 49)

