# Multivariable regression

To account for the clustering as well as to adjust for potential confounding, we will adjust the final results using a multivariable regression model. We will use generalizing estimating equations (GEE) 24 to estimate the log odds of the intervention on inappropriate treatment proportion compared to the control group. Use of GEE will allow us to adjust variance estimates (providing robust standard errors) to account for the clustering of cases within a cluster. The correlation matrix will be defined as compound symmetry. Odds ratios and 95% confidence intervals will be used to summarize the data.

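### The Mantel-Haenszel test with clusters as strata is 0/0 for any data, and neither it nor the GEE uses the matched pairs on which the trial was randomised and sized

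*Protocol*

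**What the plan says.** On design, section 4.2 states: "A study cluster will be defined as the catchment area of a community health post". These clusters are "matched in pairs according to the health facility catchment area they belong to, the distance from the health facility and the population size". It continues: "Randomization will then be done from among the matched clusters to select the intervention and the control arms". Section 4.3 gives 21 health posts per arm, so there are at most 21 pairs.

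On analysis, section 6.1 has two steps.

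- **Crude comparison.** The two arms are "compared using the Mantel-Haenszel chi-square test with clusters as strata to account for the cluster randomization". On the estimate it adds: "Crude data will be presented as cluster adjusted odds ratios and 95% confidence intervals".
- **Adjusted comparison.** Under Multivariable regression, a GEE with compound symmetry and robust standard errors is used "to estimate the log odds of the intervention on inappropriate treatment proportion compared to the control group". Under Confounding, its covariates are the independent predictors of inappropriate treatment.

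Neither step mentions the pairs or names the matching factors. Section 6.2 extends a similar analysis to secondary outcomes 1 (treatment failure) and 3 (RDT-positive proportion).

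For the Coartem outcome, section 4.3 sizes the trial on 100% against 80%: "Currently 100% of children seen with fever should receive Coartem treatment".

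**The concern.** A Mantel-Haenszel test compares the arms inside each stratum and then pools. That needs both arms in a stratum, and a cluster that was randomised whole has only one. Stratifying by cluster therefore does not allow for the cluster randomisation; it removes the comparison.

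The protocol names the test, the strata and the purpose, so this is not a detail left to a later plan. If it stands, a replacement for the crude comparison of both primary outcomes has to be chosen later, possibly with data in view. The omission of the pairs is a separate and lesser matter: the analysis does not match the way the trial was randomised and sized.

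**Working it through.** **1. The test as written.** For one stratum, let a and b be the children with and without the outcome in arm 1, c and d the same in arm 2, n1 and n2 the arm totals, m1 and m0 the outcome totals, and n = n1 + n2.

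- Expected count: E = n1·m1/n.
- Variance: V = n1·n2·m1·m0 / [n²(n−1)].
- Odds ratio: Σ(ad/n) / Σ(bc/n).

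If the cluster is wholly in arm 1, then n2 = c = d = 0 and n1 = n. So E = m1 = a, a − E = 0, V = 0, ad/n = 0 and bc/n = 0. If it is wholly in arm 2, then a = b = n1 = 0 and the same four terms are 0. Summed over 38 clusters of 12, all four totals are 0. The chi-square and the odds ratio are both 0/0, and no feature of the data changes this.

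**2. Pairs as strata instead.** Each stratum now holds both arms, so the test can be computed. Its variance still treats children in a pair as independent and leaves out the variation between the pair's two clusters. In a beta-binomial simulation under the null (20,000 trials per setting, 50% rate, assuming that matching removes none of the between-cluster variance), two-sided type I error at nominal 5% was:

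| ICC | Children per cluster | Pairs | Mantel-Haenszel by pair | Paired t-test on cluster proportions |
|---|---|---|---|---|
| 0.05 | 6 | 18 | 8.1% | 5.2% |
| 0.15 | 7 | 19 | 17.0% | 5.2% |
| 0.25 | 12 | 19 | 34.4% | 5.0% |

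These rows take the protocol's ICC label at face value. Step 3 shows that the column behaves as a coefficient of variation k. At a 50% rate, ICC = k²p/(1−p) = k², so 0.25 becomes 0.0625. The design effect for 12 per cluster is then 1 + 11 × 0.0625 = 1.6875, and the approximate error is 2[1 − Φ(1.96/√1.6875)] = 13%. At k = 0.05 the ICC is 0.0025, the design effect 1.0275 and the error about 5%. The inflation therefore ranges from negligible to large, depending on the true ICC.

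**3. What the sample size assumed.** The ordinary calculation for 50% against 70% gives 93 per arm. With design effect 1 + 11 × 0.25 = 3.75 the total is 2 × 93 × 3.75 ≈ 698, not the 456 in section 4.3. The matched-pair cluster formula, for the number of pairs c, is

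c = 2 + (1.96 + 0.8416)² × [p0(1−p0)/m + p1(1−p1)/m + k²(p0² + p1²)] / (p0−p1)²

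with the ICC column entered as k.

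- Fast breathing, k = 0.25, m = 12: bracket = 0.02083 + 0.01750 + 0.04625 = 0.08458. Then c = 2 + 7.849 × 0.08458/0.04 = 18.60, so 19 pairs, 38 clusters and 456 children, as stated.
- Fever, 100% against 80%, k = 0.25, m = 36: bracket = 0 + 0.00444 + 0.10250 = 0.10694. Then c = 22.98, so 23 pairs and 46 clusters, as stated.

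All 22 rows of the two tables come back exactly. The unmatched version (1 in place of 2) gives two clusters fewer in every row and matches none.

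**4. The GEE.** It accounts for clustering by health post and does not require both arms in a cluster. In null simulations with 42 clusters of 12, without pair terms and with ordinary robust standard errors, type I error was about 6% to 7%. Adding 21 pair fixed effects with the same standard errors raised it to roughly 18% to 20%.

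**The case against.** The strongest reply is that the Mantel-Haenszel test serves only the crude comparison. The protocol adjusts its final results with a GEE that is meant to handle clustering, and that model works. This stands. A reader might infer from step 1 that the trial has no primary result; the documents do not support that.

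A reader might also expect the analysts to drop the strata and run an ordinary chi-square, with a heavily inflated type I error. No section proposes this, and the documented alternative is the GEE. Large inflation figures would also read the ICC column as a true ICC, although the tables reproduce only when it is a coefficient of variation.

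Leaving the pairs out of the GEE is a matter of efficiency and consistency with the design; it does not by itself inflate type I error. The covariate list is open enough that facility or distance could enter, and a pair term could reasonably be left to an SAP. This stands too, and it is why the pairs are secondary to the undefined test.

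Lastly, one might say that the Coartem odds ratio must be infinite because the control value is 100%. That value is a planning assumption about what children should receive, and section 8.0 envisages inappropriate Coartem use that can fall. Non-estimability is a risk if nearly all control children are treated, not a certainty.

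None of these replies makes the Mantel-Haenszel test computable.

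**Conclusion.** The crude test in section 6.1 is undefined as written. This follows from the design alone, needs no assumption, and affects both primary outcomes and, through section 6.2, the treatment-failure comparison. Secondary outcome 3 is affected differently: no RDT is done in the control arm (section 4.2), so it has no between-arm comparison to test.

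Pairs as strata is not a repair. The size of its error depends on the true ICC and on how much variance the matching removes: about 8% to 34% if the labelled values are true ICCs, and about 5% to 13% by the design-effect approximation at 12 per cluster if they are coefficients of variation, in both cases with matching assumed to remove nothing.

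The GEE gives the trial a usable clustered analysis. What remains is a mismatch: randomisation and sample size rest on matched pairs, and neither planned analysis uses them. That the sizing was paired is inferred from the 22-row match, since the protocol does not name its formula.

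**What to change.** - **Primary outcomes.** Replace the Mantel-Haenszel test with a pair-level analysis: compute the proportion in each cluster, take the within-pair differences, and test them with a paired t-test (pairs minus 1 degrees of freedom, at most 20) or a within-pair permutation test. Report the risk difference with 95% CI. The sizing is in percentage points (50% to 70%, 100% to 80%), and for Coartem a risk difference stays estimable when an odds ratio may not.
- **Secondary outcomes.** Apply the same method to treatment failure in section 6.2, and describe the RDT-positive proportion in the intervention arm only.
- **GEE.** Keep it as supportive. Adjust for the matching factors (health facility, distance, population size) and use a small-sample variance correction. Do not add 21 pair fixed effects with ordinary robust standard errors.

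**Cost.** The change is to wording in sections 6.1 and 6.2, with no new data. The price is few degrees of freedom and some fragility: communities or CHWs may decline (sections 4.15 and 7), and losing one cluster removes its pair from the analysis.
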